**Table 1: Study Procedures Schedule**

| Week                                          | 0 | 16 |
|-----------------------------------------------|---|----|
| 3-day diet record                             | √ | √  |
| International Physical Activity Questionnaire | √ | √  |
| Clinical status and symptoms                  | √ | √  |
| Medication use                                | √ | √  |
| Height                                        | √ |    |
| Body weight*                                  | √ | √  |
| Comprehensive Metabolic Panel (CMP)           | √ |    |
| Plasma lipids and lipoproteins                | √ | √  |
| A1c                                           | √ | √  |
| Glucose tolerance testing                     | √ | √  |
| REE                                           | √ | √  |
| Postprandial metabolism (TEF)                 | √ | √  |
| Body composition                              | √ | √  |
| IMCL and hepatic lipid (pilot)                | √ | √  |
| Microbiome analysis (uBiome)                  | √ | √  |
| Endothelial function (EndoPAT)                | √ | √  |

## 4. INTERVENTION PROCEDURES

### 4.1. Intervention Diet

The interventions for the Diet and Control Groups are described below.

**The Diet Group** will be asked to follow a low-fat, vegan diet. According to the Academy of Nutrition and Dietetics, vegan and vegetarian diets meet all nutritional requirements when appropriately planned. The diet consists of whole grains, vegetables, legumes, and fruits, with no restriction on energy intake. Animal products and added oils will be excluded. In choosing grain products and starchy vegetables (e.g., bread, potatoes), participants will be encouraged to select those retaining their natural fiber and having a glycemic index <70, using tables standardized to a value of 100 for glucose. No meals will be provided. Participants will handle their own food preparation and purchases, with guidance from the research team.

The diet derives approximately 10% of energy from fat, approximately 10-15% of energy from protein, and the remainder from complex carbohydrates. The diet will provide approximately 30-40 grams of fiber per day. It is generally adequate in all nutrients except vitamin B12.

Participants will be provided with a commercially available supplement containing 100 micrograms of vitamin B12 and asked to take it daily during the study. Should they wish to continue the diet thereafter, they will be counseled to use any standard multivitamin or other reliable source of vitamin B12.

An advantage of studies such as this one, which include volunteers who are not confined to a metabolic ward or otherwise restricted, is that they can readily translate to nonclinical settings. A disadvantage is that they include a degree of uncertainty as to the extent to which participants have adhered to their prescribed diets. While this uncertainty cannot be entirely eliminated, several measures will be taken to maximize dietary adherence, based on the current investigators' published review of factors associated with dietary compliance in clinical trials. Stricter limits on fat intake, frequent monitoring of reported dietary intake, family involvement, group support, and the use of vegetarian diets are associated with a greater degree of dietary change.

**Control Group** members will be asked to continue their usual diets for the 16-week study period. Those who wish to try the intervention diet will be given instruction in the diet at the study's conclusion.

**Both groups:** For both groups, alcoholic beverages will be limited to one per day for women, and two for men.

#### **4.2. Dietary Instruction and Group Meetings**

Diet Group participants will be asked to attend weekly, one-hour group sessions for support and education. (**Class Curriculum, Appendix 8**). No weekly support or education will be provided to the participants in the Control Group.

All group sessions will be conducted by a registered dietitian, nurse, physician, cooking instructor, or research staff and will include information on nutrition, meal planning, shopping, food preparation techniques, recipes, and everyday dietary challenges, such as dining out and healthful snacking. The classes will also include education on topics such as maintaining a healthy weight, cholesterol, hypertension, diabetes, and other health issues.

For some sessions, participants will be encouraged to bring a spouse, partner, family member, or friend. To facilitate interaction between diet instructors and participants, classes will be conducted in sections of approximately 15 participants.

The curriculum is based on the investigators' prior studies and uses concepts from the Health Belief Model developed by researchers with the Public Health Service and adapted by others. This model describes constructs that predict health-related behaviors and should be considered when planning behavioral change strategies. These include perceived susceptibility, severity, benefits, and barriers, as well as cues to action, and self-efficacy. Our participants are already aware that they are overweight and may benefit from diet changes. Nonetheless, they need help in overcoming barriers

and gaining confidence in their ability to implement new dietary habits. We have therefore focused the content of the weekly support group sessions on integrating practical skills (e.g., menu planning, food preparation, dining out, healthful snacking) with their growing understanding of how dietary choices affect health. In order to facilitate individual experience with the prescribed diet, practical skills are presented early, while intellectual understanding of more complex health issues (e.g., how diet affects heart disease risk) is presented later. Each group session includes time for participants to discuss their successes and challenges, and group problem-solving is encouraged.

The study does not seek to separate the effects of the diet from those of regular group support. Rather, group support is a means of facilitating adherence. It should also be emphasized that the goal of this study is not to construct an intervention diet that is isocaloric compared with diets followed by the Control Group participants. Because the intervention diet is low in fat and high in fiber, self-selected energy intake is likely to fall as the diet period begins, and weight loss is likely.

#### **4.3. Exercise and Medication Use**

Participants in both groups will be asked to keep their level of physical exercise and use of medications constant and to add no new nutritional supplements to their current medication regimens, except as recommended by their personal physicians.

#### **4.4. Intervention Fidelity and Dietary Adherence**

**Individual meetings.** During the initial individual meal-planning meetings with the Diet Group participants, dietitians will follow a set agenda which will cover the use of vegan foods, methods for reducing dietary fat, and how to avoid proscribed foods.

**Group meetings.** To maintain intervention fidelity, the group leaders will follow a set course curriculum, using an agenda for each session and keeping a checklist of major content items to be covered at each meeting.

**Dietary Adherence.** Each participant will complete diet records at regular intervals using the methods described above. In addition, for the Diet Group, 24-hour multi-pass dietary recalls will be used to assess dietary adherence to assist study personnel in working with individuals who need additional teaching or support. The 24-hour recalls will be performed either by telephone or in person at weeks 3 and 8. These recalls will not be subjected to statistical analysis, but will allow the investigators to check for poor adherence. Such recalls have the advantage that they can be conducted at unscheduled times and over the telephone, and so are not subject to the planning and preparation required for food records. In cases where participants appear to be deviating from the prescribed diet, additional dietary counseling will be provided.

#### **4.5. Participant Retention**

Participants' interests for volunteering will be ascertained during screening. Those with reasons for volunteering other than a desire to improve their health or to advance scientific understanding may be rejected. The exclusion criteria also eliminate individuals with a history of unresolved substance abuse, which may influence retention.

Participants will be instructed that attendance at meetings is essential to study participation. The research team will take attendance at each meeting. The research staff will make phone calls to participants who do not attend.

In the weekly meetings, group support will be facilitated through group discussions and encouragement to share successes and difficulties with the prescribed diet. Meeting content will remain varied, including nutrition lectures, health education, cooking demonstrations, and opportunities to taste food. Family members will be invited to certain support group sessions. A voluntary listserv will allow Diet Group members to exchange information, recipes and ideas between meetings. Only participants, study coordinators, and the PI will be allowed to post on the list serve and the content of the list serve will be accessible only by them.

Participants who complete all assessments at weeks 0 and 16 will be paid \$100 at completion of their final assessments.

#### **4.6. Biological Specimen Handling Procedures**

Samples for the study endpoints will be drawn by a registered nurse, employed by PCRM, and will be processed at LabCorp using standard procedures.

### **5. STATISTICAL PROCEDURES**

#### **5.1. Power Analysis**

##### **Power Analysis for Overall Study**

Sample size will be based on the change in postprandial metabolism (thermic effect of food) previously observed with a plant-based diet, compared with an active dietary control. The current power analysis assumes there will be a single t-test for the comparison of the changes in thermic effect of food observed in the two study groups, with an alpha level of 0.05.

In the prior study, the change at 14 weeks for the thermal effect of food was 4.7 with an SD of 12 in the intervention arm, and 0.3 with an SD of 9.4 in the control arm. Assuming that the true treatment effect is 4.4 kcal/170 min and that the SD of the change will be 12.0 units in the Diet Group and 9.4 units in the Control Group, as previously observed, the sample size required is 96 per arm (192 total) for 80% power, 109 per arm for 85% power, 128 per arm for 90% power.

However, if this magnitude of treatment effect is assumed to be present at the same magnitude of effect at each of the 5 evaluation points used in TEF assessment and assuming that the standard deviation is about 10.85 points for all observations, with 5 observations per participant, correlated at a magnitude of 0.7 with each other, the sample size required is 73 participants per arm (146 total) with 80% power, 83 per arm with 85% power, 98 per arm for 90% power.

Assuming an attrition of 10%, the required sample size is 81 per group, or 162 total for 80% power.

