### **5.3. Statistical Analysis**

Descriptive statistics for all demographic variables and clinical measures will be calculated for each group. To determine if there are statistically significant differences between the 2 groups at baseline, t-tests will be calculated for continuous measures and chi squares will be calculated for categorical measures. Regardless of any differences, baseline values for key outcome variables will be included as covariates in the main assessments of the effect of diet in the multivariate analysis of covariance. An alpha of 0.05 will be used for all statistical tests.

For nutrient intake and physical measures, descriptive statistics (means, standard deviations, tests for normality) will be calculated. If data are normally distributed, parametric tests for significant effects will be used; for non-normally distributed variables, non-parametric tests will be used.

The initial test of the hypotheses will be examined by performing t-tests for independent samples on the difference score denoting the change from baseline to the reporting period. For missing data in a reporting period, values from the previous period will be brought forward. For body weight, drop-outs will be considered to have returned to baseline weights.

**5.4. Assessment of Diet Adherence.** Diet-and-supplement group participants will be described as adherent or non-adherent based on whether they met the following criteria: absence of proscribed foods reported on 24-hour recalls and diet records, saturated fat <5% and total fat <25% of energy, and average daily cholesterol intake <50 mg on 3-day dietary records.

For drop-out rates, we will determine if there are between-group differences, using chi-square.

**5.5. Assessment of Medication use.** Any changes to lipid-lowering medications will be classified as a net increase, net decrease, or mixed (changes in opposing directions for 2 or more medications). Using chi-square, we will determine whether there are differences in medication changes between the 2 groups.

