## **6. TIME LINE AND PARTICIPANT FLOW**

### **6.1. Time Line**

The study will be conducted in six cohorts, each including 40 participants, over a 3-year period.

For the first cohort, recruitment will take place October 2016 – January 2017. The intervention, including weekly meetings, will take place between February and May 2017 for a total of 16 weeks. For the second cohort, recruitment will take place in December 2016 and January, 2017. The intervention, including weekly meetings, will take place between March and July 2017. Similar time frames will apply in the two subsequent years.

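### Section 5.1 says it sizes for a single t-test (96 per arm) but adopts 73 per arm through a five-reading discount that the protocol does not support; 162 enrolled gives about 69% power for that test, and section 6.1 plans 240

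*Protocol*

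**What the plan says.** Section 5.1 of the protocol opens by stating what its sizing rests on: it "assumes there will be a single t-test for the comparison of the changes in thermic effect of food observed in the two study groups", at alpha 0.05. The inputs come from a prior study: "Assuming that the true treatment effect is 4.4 kcal/170 min", and "the SD of the change will be 12.0 units in the Diet Group and 9.4 units in the Control Group". For that test the section gives 96, 109 and 128 per arm for 80%, 85% and 90% power.

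The next paragraph supposes that the same effect is present at each of five TEF evaluation points, with an SD of about 10.85 for every observation and a correlation of 0.7 between observations. On that basis "the sample size required is 73 participants per arm (146 total) with 80% power", with 83 and 98 per arm for 85% and 90%. With 10% attrition, "the required sample size is 81 per group, or 162 total for 80% power".

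Three other places bear on this:

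- Section 3.6 schedules post-meal metabolic rate at two times, 2 and 4 hours after the test meal, following a fasting measurement.
- Section 5.3 makes the first test of the hypotheses by "performing t-tests for independent samples on the difference score". It also says that baseline values will enter the main assessments as covariates.
- Section 6.1 states: "The study will be conducted in six cohorts, each including 40 participants". That is 240 in total.

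**The concern.** Within one section, 96 per arm and 73 per arm are both offered as the size for 80% power, and the enrolment figure is built on the smaller. The smaller one depends on a gain from averaging five correlated readings. The test named in 5.1 and again in 5.3 takes one change score per person, and the protocol does not schedule five readings from which such a score could be averaged.

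The SD is also doubtful. The value 10.85 is close to the root-mean-square of 12 and 9.4. Those are SDs of the TEF change, and the effect is expressed in kcal per 170 minutes, which suggests one summary value per person. If so, an averaging discount has been applied to a quantity that is already a summary.

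What is at stake is the stated power for a primary variable. Anyone who takes 162 as the recruitment target would believe the trial has 80% power for the assumed effect when the named test does not have it. The document also leaves unclear whether the target is 162 or 240.

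**Working it through.** **Inputs.** All are from the protocol. Section 5.1: effect 4.4; SDs 12.0 and 9.4; alpha 0.05; five readings; SD 10.85; correlation 0.7; attrition 10%. Section 3.6: two post-meal readings. Section 6.1: 6 × 40. Sidedness is not stated. Two-sided reproduces the protocol's figures; one-sided does not (75 per arm instead of 96).

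**1. Reproduce the single t-test.** Root-mean-square SD = √[(12² + 9.4²)/2] = √116.18 = 10.78. The normal approximation n = 2(1.96 + z)² × 116.18 / 4.4² gives 94.2, 107.8 and 126.1 for 80%, 85% and 90% power. The noncentral t gives 96, 109 and 128, exactly as stated.

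**2. Reproduce the five-reading figure.** The mean of five readings correlated 0.7 has variance factor (1 + 4 × 0.7)/5 = 0.76. Then n = 2(1.96 + z)² × 10.85² × 0.76 / 4.4² = 72.5, 83.0 and 97.1, matching the stated 73, 83 and 98. So the step from 96 to 73 is the factor 0.76.

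**3. Attrition.** 73/0.9 = 81.1. The protocol gives 81 (82 if rounded up, a trivial difference). Conversely, 81 × 0.9 = 72.9, or about 73 evaluable per arm.

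**4. Power of the named test.** Unadjusted, two-sided 0.05, effect 4.4, SDs 12 and 9.4, noncentral t:

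| Evaluable per arm | Corresponds to | Power |
|---|---|---|
| 73 | 162 enrolled, 10% attrition | 68.8% |
| 81 | 162 enrolled, no attrition | 73.3% |
| 96 | 96/0.9 = 106.7, so 107 per arm, 214 enrolled | 80.3% |
| 108 | 240 enrolled (120 per arm), 10% attrition | 84.8% |

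The normal approximation gives 69.4% at 73 per arm. With the SD set to 10.85 the noncentral t gives 68.2%. If the 10% who drop out are instead kept at zero change, as the carry-forward rule in 5.3 implies for TEF, power with 81 per arm analysed is again about 68%.

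**5. Grant the averaging argument but use the scheduled readings.** With two readings the factor is (1 + 0.7)/2 = 0.85. Then n = 2(1.96 + 0.84)² × 10.85² × 0.85 / 4.4² = 81.1, so 82 evaluable per arm. At 73 per arm power is about 75%.

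**The case against.** Four points can be made for the plan.

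*A t-test does not in itself rule out the discount.* A single t-test on each person's mean of five readings would have exactly the 0.76 factor, provided 10.85 is a per-reading SD. This is correct. The case therefore rests on the schedule and the SD as well as on the form of the test: section 3.6 provides two post-meal readings, and the protocol gives no source for 10.85 as a per-reading value or for the correlation of 0.7.

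*Double-counting is not proved.* A reader might infer that the averaging gain has certainly been taken twice. The documents do not establish this. The unit and the closeness of 10.85 to 10.78 make it plausible, but 10.85 equals neither the root-mean-square (10.78) nor the simple mean (10.70) of the two SDs. How those SDs were formed lies in the cited prior study.

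*The main assessment is baseline-adjusted.* Section 5.3 calls the t-test only the initial test, so 69% is not the power of every planned analysis. Adjusting for baseline multiplies the change-score variance by (1 + r)/2, where r is the correlation between baseline and follow-up. The protocol gives no r. As an assumed range, 73 per arm would have about 81% power at r = 0.5, 76% at r = 0.7 and 73% at r = 0.8. Some power may be recovered, but section 5.1 claims none from this source and sizes explicitly for the t-test.

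*The scheduled enrolment is adequate.* A reader might infer that the trial is underpowered or that recruitment would end at 162. Nothing in the protocol says so. Section 6.1 plans 240, and a required minimum of 162 could coexist with a plan for more. This limits the consequence but leaves the 80% claim at 162 uncorrected. Nor can 240 be taken as the justified target, because no power calculation in the protocol yields it. Section 3.2 was not in the text available, so whether it addresses enrolment could not be checked.

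**Conclusion.** The point stands in limited form. The 80% power stated for 162 enrolled is not supported by the test, the readings or the SDs that the protocol describes. For the unadjusted two-sided t-test on the stated effect and SDs, with 10% attrition, power at 162 is about 69%. It is about 75% if two readings are averaged on the protocol's own assumptions. Eighty per cent needs 214 enrolled, and the 240 in section 6.1 gives about 85%.

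The calculation of 73 is not itself in error; the fault is that its assumptions do not match the rest of the document. The shortfall applies only if 162 is the operative total, and 69% describes the t-test for which 5.1 says it sizes, not the baseline-adjusted analysis. The mismatch between 162 and 240 needs resolving in either case.

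**What to change.** In section 5.1, remove the five-reading calculation and the 146 and 162 totals as the basis for 80% power. Alternatively, keep that approach but justify it with a sourced per-reading SD and correlation, the number of readings actually scheduled in section 3.6, and an analysis that averages or jointly models them.

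Then reconcile section 5.1 with section 6.1 and state one enrolment total with its power under the planned test. If the total is 240, that is about 85% (108 evaluable per arm after 10% attrition, difference 4.4, SDs 12 and 9.4). If it is 162, it is about 69%. If the sponsor wishes to count on baseline adjustment, 5.1 should say so and give the assumed correlation.

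The cost is a change of protocol wording. No participants beyond those planned in section 6.1 are needed.

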### **Power Analysis for Intracellular Lipid Substudy**

Two studies, cited above, provide a basis for a power analysis for the substudy assessing the role of intramyocellular and hepatic lipid on insulin sensitivity and, ultimately, postprandial metabolism. In the 2012 Yale study, 7 lean, young insulin-resistant individuals whose parents had type 2 diabetes followed a hypocaloric (1200 kcal/d) diet for 9 weeks, leading to an average weight loss of  $4.1 \pm 0.6$  kg. During this intervention period, average intramyocellular lipid fell approximately 30%, from  $1.1 \pm 0.2\%$  to  $0.8 \pm 0.1\%$ . In an observational study including 21 individuals following vegan diets and 25 following omnivorous diets, soleus muscle intramyocellular lipid for the vegan participants was found to be 11.7 (6.1–24.6), compared with 16.9 (2.7–44.7) for the omnivorous participants ( $P = 0.01$ ). The 95% confidence interval for the difference was reported to be -13.2 to -3.3).

Based on the Yale study, assuming a change in IMCL of 0.3 percentage points with a standard deviation of 0.2 and, in the control arm, a mean change of zero with a similar standard deviation, to have 90% power to detect a difference of this magnitude between the two arms would require 11 subjects per arm. Ten per arm would yield 88% power.

Because this is an exploratory substudy and variability in response to the diet is largely unknown, we aim to include 20 participants per arm in the substudy, for a total of 40 participants.

### **5.2. Data Management**

All laboratory samples, reports, questionnaires, and data sheets will be coded with participant identification numbers, rather than names. Laboratory reports will be delivered to the PCRM office at [name], where they, along with all other history and data forms, will be maintained in individual participant files in a locked cabinet.

Data will be promptly entered into the data tables at PCRM using Microsoft Excel. Two research staff members will check the tables for accuracy against the original documents. Data tables will be routinely copied onto back-up files and stored for safety on an off-site, passcode-protected, secure server. Data grids will be sent electronically to the biostatistician for analysis. Registered dietitians will be provided with information

on usual ranges for nutrients or intakes of interest and asked to check their original data and analysis for errors if they fall outside of these ranges.

